### Study progress

The study protocol has been approved by the French ethic authorities (see “Declarations” section below). Procedures and contracts for access to the SNDS databases are in progress. Data management and analyses will start in the second half of 2021, and the main results will be published in 2022.

## Discussion

We will conduct a large RWE study to investigate the risk of major clinical outcomes and economic impact of routine CAD screening in individuals with T2DM and a very high risk for cardiovascular disease in France. We will perform a retrospective analysis using the electronic health record (EHR) data from the SNDS databases which represent almost the entire French population allowing us sufficient sample size to address the investigated question.

### Screening for silent CAD and risk of major cardiovascular events

Previous RCTs demonstrated no clinical benefit associated with routine CAD screening in asymptomatic T2DM patients, but population with a high cardiovascular burden and any organ vascular damage has not been investigated [11–14]. Also, the observed incidence of outcomes was much lower than expected in published RCTs evaluating the interest of routine CAD screening in individuals with T2DM (Table 1). The conduction of a new prospective RCT will be too expensive, time-consuming with difficulties for recruiting asymptomatic participants with a very high cardiovascular risk. Indeed, the DYNAMIT (Do You Need to Assess Myocardial Ischemia in Type-2 diabetes) study was stopped prematurely due to difficulties in recruitment of participants and a low incidence of cardiovascular events [12]. DYNAMIT included only one-fifth (631/3000) of the originally planned enrolment to detect a 20% relative risk reduction (RRR) in the primary endpoint (a composite of all-cause death, non-fatal myocardial infarction, non-fatal stroke, or heart failure requiring hospitalization or visit to emergency department) in people with T2DM at a high cardiovascular risk (aged 55 to 75 years with at least 2 other cardiovascular risk factors). A recent meta-analysis estimated that a large number of participants would be needed to demonstrate a potential benefit of the systematic CAD screening strategy to reduce the incidence of major cardiovascular events [15]. The optimal sample size for 20% RRR of major cardiac events should be 29,763 participants (19,548 for all-cause death). Therefore, a retrospective RWE study seems to be an appropriate approach to evaluate the long-term cost-effectiveness of systematic CAD screening strategy in T2DM subjects at a very high cardiovascular risk without known history of CAD. Of note, among 3.7 million people with diabetes in France, we estimate that at least 90,000 individuals will be eligible for our study in the SNDS database.

### Cost-effectiveness of routine CAD screening in patients with diabetes

Systematic CAD screening strategy leads to more invasive examination, especially coronary angiography, which is associated with increased risk of complications [11, 12]. Routine CAD screening encourages also revascularizations and intensification of pharmacological treatments, despite uncertainties in terms of related benefits. In the FACTOR-64 study, CAD screening was not associated with a significant reduction in major cardiovascular events despite intensive pharmacological control of cardiovascular risk factors (and some coronary revascularizations) in patients with a positive screening test, while individuals assigned to control group and those with a negative screening test had only conventional cardiovascular treatment goals [13]. Furthermore, BARDOT (Basel Asymptomatic high-Risk Diabetics' Outcome Trial) study showed that combined medical therapy and invasive strategy (coronary angiography followed or not by revascularization) for silent CAD, compared with medical treatment alone, was associated with reduced scintigraphic CAD progression, but no significant difference was observed in terms of hard clinical events in high risk T2DM patients [28]. Therefore, to avoid unjustified health expenses and misuse of collective resources associated with routine CAD screening, we conduct the SCADIAB study to assess the cost-effectiveness of this strategy in people with T2DM and a very high cardiovascular risk.

### Strengths and limitations

The key strength of our study is the collection of a comprehensive range of clinical features, cardiovascular procedures, history of pharmacological therapies or surgery, major events and survival status in the whole French population of patients with T2DM and a very high cardiovascular risk during an overall period of 12 years. SCADIAB findings will have a broader generalizability for all T2DM patients at a very high cardiovascular risk. Our study will provide a line of complementary evidence (further to RCTs’ findings) in terms of routine CAD screening in a contemporary cohort of patients with T2DM in real-world settings. SCADIAB will be more economical and time efficient than RCT, but a number of intrinsic limitations need to be acknowledged. The retrospective and non-randomized design of our study is subject to bias (selection, information, detection) and confounding factors. To limit selection bias, our study population will be rigorously defined using pre-specified inclusion criteria (T2DM for at least 7 years, with at least 2 cardiovascular risk factors and one or more organ damage) extracted from reliable and valid SNDS database. The 7-year selection period leading to assignment of each individual to one of the two study arms (CAD screening or absence of CAD screening) will limit information bias. We will use validated algorithms to identify inclusion criteria and endpoints [29–31]. Also, the cardiovascular investigation required for study arms assignment (stress test, scintigraphy, stress echocardiography…) will be recorded exhaustively in the SNDS database. We believe that the detection bias will be limited in our study as we have access to the SNDS database covering the whole French population including death registry. Finally, we will use the hdPS method to control measurable confounding factors as well as unknown or unmeasurable ones [32–34].

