**Methods:**

SCADIAB is a comparative nationwide cohort study using data from the French National Health Data System. The main inclusion criteria are: age ≥ 40 years, DT2 diagnosed for ≥ 7 years, with ≥ 2 additional cardiovascular risk factors plus a history of microvascular or macrovascular disease, except CAD. We estimated ≥ 90,000 eligible participants for our study. Data will be extracted from 01/01/2008 to 31/12/2019. Eligible participants will be identified during a first 7-year selection period (2008–2015). Each participant will be assigned either in experimental (CAD screening procedure during the selection period) or control group (no CAD screening) on 01/01/2015, and followed for 5 years. The primary endpoint is the incremental cost per life year saved over 5 years in CAD screening group *versus* no CAD screening. The main secondary endpoints are: total 5-year direct costs of each strategy; incidence of major cardiovascular (acute coronary syndrome, hospitalization for heart failure, coronary revascularization or all-cause death), cerebrovascular (hospitalization for transient ischemic attack, stroke, or carotid revascularization) and lower-limb events (peripheral artery disease, ischemic diabetic foot, lower-limb revascularization or amputation); and the budget impact for the French Insurance system to promote the cost-effective strategy. Analyses will be adjusted for a high-dimension propensity score taking into account known and unknown confounders. SCADIAB has been funded by the French Ministry of Health and the protocol has been approved by the French ethic authorities. Data management and analyses will start in the second half of 2021.

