### Study population

#### Inclusion criteria

Eligible participants must meet all of the following criteria:Age = 40 years or older,Affiliation to the general health insurance scheme in France,Diagnosis of T2DM,Duration of T2DM ≥ 7 years,Two or more additional cardiovascular risk factors (obesity, hypertension, hypercholesterolemia, or tobacco smoking using the chronic obstructive pulmonary disease (COPD) as a proxy),At least one microvascular or macrovascular disease: carotid stenosis, transient ischemic attack (TIA), stroke, lower-limb peripheral artery disease (PAD), CKD, severe diabetic retinopathy with requirement of laser photocoagulation, or peripheral or autonomic diabetic neuropathy.

Diagnosis will be determined based on the list of 100% health insurance coverage for chronic diseases in France (including T2DM, hypertension, TIA, stroke, PAD, CKD, COPD), the history of diseases of interest or surgery (coronary, carotid or lower-limb revascularization, bariatric surgery, kidney transplantation) according to the International Classification of Diseases Code Tenth Revision (ICD-10) (Additional file 1: Table S1), or at least 3 deliveries of one or more corresponding drugs as appropriate (antidiabetic, anti-obesity, antihypertensive or lipid-lowering drugs) over one year.

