#### Exclusion criteria

One of the following:The presence of CAD (defined as a history of acute coronary syndrome, coronary revascularization, angina pectoris, or unstable angina).Any visit to an emergency department for chest pain resulting for admission to a cardiac intensive care unit.

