### Statistical analysis plan

The data will be analysed by the biostatistician of the “Clinical Epidemiology Unit” of the University Hospital of Bordeaux (USMR). Analyses will be performed using SAS® software, version 9.4 or later (SAS Institute, Cary, NC, USA, http://www.sas.com) and all tests will be performed at the first-order error risk α = 5%. The flow-chart (CONSORT), as well as the characteristics of patients at inclusion (eligibility criteria, epidemiological, clinical, biological characteristics and treatment use) will be presented. Confounding factors will be taken into account through a hdPS score that will involve around 500 variables, according to the Bross formula [26]. A principal component analysis will then allow us to reduce the dimensionality to 30 components, and the goodness of fit of this hdPS score will be estimated by a graphical comparison of the score distribution and by standardized mean differences between the two study groups [27]. Comparisons between the two groups will be carried out with and without adjustment for the hdPS score, and the hypotheses of the different regression models chosen, will be systematically verified.

Regarding the analysis of the primary endpoint, a gross estimate of the incremental cost per life-year gained at 5 years will be conducted. The confidence interval (CI) of this incremental cost-effectiveness ratio will be estimated by boostrap (5000 iterations). The analysis will be performed as Intent to Treat. To investigate a possible relationship between the frequency of screening and survival, we will define four different subgroups: screening conducted at least once a year, less than once a year (and at least once every two years), less than once every two years (and at least once every three years), and only once during the follow-up period.

A cost-consequence analysis will be performed linking results of all direct costs (observed during the following period) and results on major cardiovascular events. A budget impact analysis will be conducted to determine the public expenses of the spread of a systematic screening for silent ischemic CAD.

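### The article says the hdPS controls unknown and unmeasurable confounders; it reaches only recorded variables and what they proxy, and the described diagnostics cannot show what remains

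*Protocol article*

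**What the plan says.** The claim appears twice. Under Strengths and limitations: "we will use the hdPS method to control measurable confounding factors as well as unknown or unmeasurable ones". In the Abstract, under Methods, in softer terms: "Analyses will be adjusted for a high-dimension propensity score taking into account known and unknown confounders".

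The Statistical analysis plan section describes what the score is made of: "Confounding factors will be taken into account through a hdPS score that will involve around 500 variables, according to the Bross formula", followed by "A principal component analysis will then allow us to reduce the dimensionality to 30 components". The section on recruitment and follow-up adds that every variable needed for the score is measured in the selection period before 1 January 2015, and the only data source is a national claims database.

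Two checks bearing on confounding are described. One is a "graphical comparison of the score distribution and by standardized mean differences between the two study groups". The other is a contrast of results: "Comparisons between the two groups will be carried out with and without adjustment for the hdPS score".

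On exposure, the Screening group section assigns a patient to screening on the strength of at least one listed procedure code, with no condition on the reason for the test. The Exclusion criteria remove known coronary disease, including angina, and "Any visit to an emergency department for chest pain resulting for admission to a cardiac intensive care unit". In the Inclusion criteria, the smoking risk factor is defined as "tobacco smoking using the chronic obstructive pulmonary disease (COPD) as a proxy".

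**The concern.** A propensity score, high-dimensional or not, is a function of the variables put into it. It balances those variables. It also reduces imbalance in an unrecorded factor to the extent that recorded codes stand in for that factor, which is the rationale for using hundreds of codes. A factor with no trace in the codes is not balanced. To say without qualification that unknown or unmeasurable confounders are controlled gives the method a property it does not have.

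The hdPS is the main safeguard in a non-randomised comparison, and the Conclusions section expects the findings to inform payers, clinicians and future recommendations. Why a stress test was ordered is a plausible confounder here. Outpatient symptoms that were never coded as angina and never led to cardiac intensive care do not exclude a patient, so a test done for them counts as screening. If the adjusted survival result is read as free of unknown confounding, a modest difference in either direction could be taken as an effect of screening when it reflects who was tested and why. The same error would pass into the life-years term of the primary endpoint.

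**Working it through.** **1. Does the described score contain anything unrecorded?** No. Its inputs are about 500 variables measured in the selection period. Ranking by the Bross formula uses the prevalence and outcome association of each candidate, so it can rank only recorded candidates. Principal components are combinations of those same variables, so reducing to 30 components adds no information. Unrecorded factors enter only through their correlation with recorded ones.

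**2. Can the described diagnostics show what is left?** Score distributions and standardized mean differences (SMDs) are computed on recorded variables. A simulation illustrates this; all its parameters except the sample size are assumptions.
- Sample size: 90,000, the article's estimate of eligible patients, which reproduces as 2.4 million × 0.38 × 0.10 = 91,200.
- True rate ratio 1; 5-year follow-up; baseline rate 0.04 per year.
- One unmeasured factor, with log-odds −0.4 per SD for being screened and log-hazard +0.5 per SD.
- A propensity score on 21 measured covariates, one of them a proxy for the unmeasured factor, applied by inverse-probability weighting. This simplifies the planned hdPS adjustment. Each row is a single run.

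| Correlation of proxy with unmeasured factor | Crude RR | Adjusted RR | Largest SMD, measured variables | SMD, unmeasured factor |
|---|---|---|---|---|
| 0 | 0.90 | 0.82 | 0.0005 | −0.39 |
| 0.3 | 0.92 | 0.85 | 0.0007 | −0.35 |
| 0.6 | 0.90 | 0.87 | 0.0010 | −0.26 |
| 0.9 | 0.92 | 0.97 | 0.0011 | −0.08 |

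Measured balance is near perfect in every row, yet the adjusted ratio is close to the true value of 1 only when the proxy is very good. Comparing crude with adjusted results does not reveal the problem either: in the first row both are wrong, and the adjusted one is further from 1.

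**3. How large could the bias be?** The article gives no figure for residual confounding, so the inputs are assumed: a factor present in a share p1 of screened and p0 = 10% of unscreened patients, with risk ratio RR for death. Bross bias factor = [1 + p1(RR − 1)] / [1 + p0(RR − 1)].

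| p1 | RR 1.5 | RR 2.0 |
|---|---|---|
| 20% | 1.10/1.05 = 1.05 | 1.20/1.10 = 1.09 |
| 30% | 1.15/1.05 = 1.10 | 1.30/1.10 = 1.18 |
| 40% | 1.20/1.05 = 1.14 | 1.40/1.10 = 1.27 |

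For scale, a 20% relative risk reduction corresponds to 1/0.80 = 1.25. Only one of the six cells reaches it. At that cell a true ratio of 0.80 would appear as 0.80 × 1.27 = 1.02.

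**4. The other direction.** If the harmful factor is less common in screened patients and the true effect is null:
- 45% vs 55%, RR 1.5: 1.225/1.275 = 0.96
- 40% vs 60%, RR 2: 1.40/1.60 = 0.875
- 30% vs 60%, RR 3: 1.60/2.20 = 0.73

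**5. E-values.** For an apparent ratio of 0.80, with r = 1/0.80 = 1.25, the E-value is r + √[r(r − 1)] = 1.25 + √(1.25 × 0.25) = 1.81. For 0.85 and 0.90 it is 1.63 and 1.46.

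**The case against.** Much of the other side is sound.

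- *The hdPS does reach some unmeasured confounding.* True, and the last row of the simulation shows it. A reader who concludes that a propensity score does nothing for unmeasured factors goes too far. Partial reduction through proxies is still not control of the unmeasurable. The Abstract's wording is softer than that of the limitations section but makes the same kind of claim.
- *The article already admits bias and confounding.* It does, in general terms, and it calls its evidence complementary to randomised trials. But it then closes by offering the hdPS as the remedy for unknown confounding too, which takes back the part of the caveat that matters here.
- *Nothing says that no residual-confounding check is planned.* Correct. A reader might infer that the authors omit such a check because they believe the hdPS makes it unnecessary. No sentence makes that link, and a condensed article may leave sensitivity analyses to a full plan that is not shown. What the text supports is narrower: the checks it does describe cannot detect what remains.
- *COPD is an eligibility proxy.* Also correct. A reader might infer that smoking is visible to the study only through COPD. The Inclusion criteria do not say so, and other smoking-related codes may be among the 500 variables.
- *The illustration does not show a spurious 20% benefit from symptoms.* It does not. Symptoms more common in the screened group raise its apparent mortality. The 20% figure is the planning effect of an earlier trial and the sample-size target of a meta-analysis, both cited in the Discussion; it is not this study's target.

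**Conclusion.** The statement is wrong as written in both places and should be corrected. The score controls measured confounders and, partly, those proxied by recorded variables; the diagnostics described do not show what is left over. The point bears on what the study may conclude, because test indication is not part of the group definition.

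On assumed inputs only, the bias factor for one unrecorded factor more common in screened patients is 1.05–1.27. For symptoms that works against screening, and it matches a 20% relative risk reduction only at the top of the range. A factor less common in screened patients would favour screening, with apparent ratios of 0.96 down to 0.73 under the other assumed inputs. The documents do not indicate which pattern applies, so neither range is an estimate of the actual bias. This is a change that should be made. It does not show that the planned analysis is invalid.

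**What to change.** 1. In the Abstract and in Strengths and limitations, say that the hdPS adjusts for measured confounders and for those proxied by recorded variables, and drop the claim about unknown or unmeasurable ones.
2. Name residual confounding, in particular by test indication and smoking, as a limitation that qualifies the conclusions.
3. If the full plan contains no such analysis, prespecify a negative-control outcome not plausibly affected by coronary screening, run through the same hdPS model, and an E-value or Bross bias analysis on the survival result with its assumed inputs and direction stated.

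The cost is a few sentences and one or two extra runs on the same data extraction. The downside is a less favourable claim for the method.

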## Conclusions

SCADIAB study is the first investigation of the cost-effectiveness of CAD screening strategy in T2DM patients with a very high cardiovascular risk. It will evaluate the economic impact and clinical benefits of routine CAD screening in this population. It will also evaluate the clinical practice regarding CAD screening. SCADIAB will provide essential information for payers, clinicians, and scientific societies in terms of long-term efficiency of systematic CAD screening in a large T2DM population. Our study will also measure the economic performance of CAD screening in a real-world setting, with an accurate comparison with no CAD screening strategy. The SCADIAB findings will help to optimize the use of health care resources and guide clinical decision-making and future recommendations.

## Data Availability

Not applicable.

## Abbreviations

BARDOT: Basel Asymptomatic high-Risk Diabetics' Outcome Trial
CAD: Coronary Artery Disease
CCAM: *Classification Commune des Actes Médicaux* (The French classification of medical procedures)
CI: Confidence Interval
CKD: Chronic Kidney Disease
COPD: Chronic Obstructive Pulmonary Disease
DYNAMIT: Do You Need to Assess Myocardial Ischemia in Type-2 diabetes
EHR: Electronic Health Record
ESKD: End-Stage Kidney Disease
HDPS: High-Dimension Propensity Score
ICD-10: International Classification of Diseases Code Tenth Revision
PAD: Peripheral Artery Disease
RCT: Randomized Controlled Trial
RRR: Relative Risk Reduction
RWE: Real-World Evidence
SCADIAB: Cost-effectiveness of Screening of Coronary Artery disease in patients with type 2 DIABetes at a very high cardiovascular risk
SNDS: *Système National des Données de Santé* (The French National Health Data System)
T2DM: Type 2 Diabetes Mellitus
TIA: Transient Ischemic Attack
